### Methodological Challenges

Recruitment of eligible participants presents the main challenge for this study. However, based on estimations of the prevalence of MS in Germany as well as pregnancy and relapse rates, our sample size represents only ~0.8% of the total target population in Germany. The close cooperation with the *German MS and Pregnancy Registry*, founded by members of the study group, gives us access to a database of more than 3,000 pregnancies of women with MS. Several MS clinics and surgeries across Germany, as well as the German Society for MS (DMSG) support recruitment efforts by sharing flyers and online adverts with their patients or members, and searching their databases for potential participants. The ongoing COVID-19 pandemic presents another challenge which slowed down recruitment and testing, particularly in the first quarter of 2021. In accordance with the rules and recommendations of the German government, we have implemented a strict hygiene plan for participants and researchers to continue with recruitment.

The TSST-C is vulnerable to subjective factors in the examination committee and environmental factors. The procedure is guided by detailed protocols and pilot runs, to ensure standardization within and between study centers. The same investigator performs neuropsychological testing in both study centers, granting further consistency of conditions.

To account for the vulnerability of the study population and potential anxiety around measures such as MRI or blood sampling, we devised detailed, child-friendly participant education material. The children's guardians are usually present and the child is offered a topical local anesthetic in preparation for the drawing of blood.

In this study, antenatal or postnatal stressors may act as confounders. Maternal psychosocial stress during pregnancy has been shown to elicit increased maternal and fetal cortisol levels (54, 55). It is further associated with an increase in the offspring stress response, disturbed motor and structural brain development and an increased risk of cognitive, behavioral, and emotional problems in later life, such as autism spectrum disorders, ADHD, depression and schizophrenia (for reviews see (9, 55)). MS relapses are not only treated with GCs but also are a major psychological stressor. However, as relapses during pregnancy rarely go untreated, there is no realistic way of mitigating this confounder using an untreated MS control group. Due to the retrospective nature of this study, there is no reliable method to assess perceived psychological stress level beyond major stressful life events, at a minimum of 8 years in the past. The mother's stress level during pregnancy is thus estimated using a questionnaire based on the Stress and Adversity Inventory (STRAIN) (56), which was adapted to this study's context. Additionally, the children fill out a questionnaire regarding subjective and objective stress in the past 12 months (see Table 1).

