## Introduction

### Background

Multiple sclerosis (MS) is one of the most common neurological diseases in young adults, usually occurring between the ages of 20 and 40 years, affecting an estimated 2.8 million patients worldwide (1). Approximately two thirds of these patients are women, mainly of childbearing age (2). Therapy for MS consists of disease-modifying therapy (DMT) for relapse prophylaxis with immunomodulatory substances and relapse therapy with methylprednisolone (MP). As most immunomodulators are not approved for use during pregnancy, treatment is usually discontinued with a subsequent risk increase for relapses (3). While the risk for relapses especially during the first and second trimester is comparable to the prepartum period and thus not an uncommon event, the risk decreases by ~70% during the third trimester (4). Based on these data and the prevalence rate for MS in women of childbearing age (1), we estimate that in Germany ~5,500 MS-relapses occur annually during a pregnancy.

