### Research Aims and Hypotheses

This study is based on two hypotheses: Fetal exposure to MP during MS relapse therapy leads to epigenetically mediated

a. disturbances in functional and structural brain development andb. a long-term change in stress sensitivity of the offspring.

The resulting changes in brain function are associated with neuropsychiatric abnormalities as well as cognitive and behavioral changes in later life.

The primary objective of this cross-sectional study is to elucidate associations of antenatal MP exposure with cognitive performance in children aged 8–18 years compared to non-exposed children of mothers with MS. As secondary objectives, this study will investigate the association of cognitive development and behavioral problems with underlying changes in stress sensitivity and functional and structural brain development. To clarify potential epigenetic mechanisms underpinning these changes in stress sensitivity and functional and structural brain development, DNA methylation at the promotor region of the GC receptor gene *NR3C1* and at the H19/IGF2 locus, which controls expression of the insulin-like growth factor 2 (IGF2), the major growth hormone during development (38), will be investigated. To elucidate further potential mechanisms, changes in the composition of the microbiome will be examined.

This study is expected to advance the understanding of developmental programming effects of antenatal high-dosage GC exposure. Another major aim of this study is to add data to the debate around evidence-based decision-making regarding (1) the continuation of a DMT during pregnancy *vs*. the potential long-term risks of relapse therapy with MP for the child's cognitive and neuropsychiatric health in later life, and (2) the risks of relapse treatment with MP for the child *vs*. the risks of an untreated relapse for the mother. There is an accumulating amount of *real world* data on the safety of continuing a DMT during pregnancy primarily with interferons or glatiramer acetate, which may be safer for mother and child than a potentially necessary relapse treatment with MP.

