### Sample Size

The aforementioned study by some of the authors (11) investigated cognitive performance, as measured by an IQ test, in two groups of 39 healthy children at the age of 8 years. Considering the lower biological activity of MP compared to BM, the cohort in the present study was exposed to a GC-dose up to 50-fold higher than in the study on the effects of BM. The higher dosage of MP will most likely expose a significant effect in two groups of the same size as the previous study.

As the present study uses a different IQ test, the planned sample size is further based on the standardized effect size Cohen's *d*, as a multiple of the standard deviation. The previous study found a mean difference in IQ score of 10.5 points (SD = 14.0). A two-sample *t*-test (α = 0.05) would have sufficient power of 82% (*d* = 0.71) to 87% (*d* = 0.75) with two groups of 35 children. This takes into account potential non-evaluability of five participants per group, e.g., in the case of artifacts or attrition. The planned regression models include seven variables, which, based on the *rule of ten* leads to a sufficient number of cases to produce robust results (39).

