Demographic data of participant and guardian(s)	Demographic and socioeconomic data are collected from the participants and their guardian(s) with questionnaires and an interview, including age, sex, height, weight, guardians' education (highest degree), marital status, and chronic health conditions. Collected on NPT day.
Basic pregnancy and birth data	Pregnancy week at time of relapse and treatment is recorded for children exposed to GC. Birth data for the child (gestational age at birth, birth weight and length, head circumference at birth) and mother (diabetes mellitus and pre-eclampsia) are collected via an interview and the consultation of medical files. Collected on NPT day.
MS-specific medical data	To describe the mother's MS status during pregnancy, medical files and the mother are consulted regarding disease course and duration, therapies, and disease progression. Collected on NPT day.
Stressors during pregnancy (mother)	Based on similar validated instruments, a questionnaire adapted to this study's aims is used to assess stress during the pregnancy. For each trimester, the mother indicates any stressors related to personal, familial, or work life, or noxious substances intake. Collected on NPT day.
Recent stressors (child)	A German self-report questionnaire is used to determine stressful life events in the past 12 months of the child's life (Zürcher Life Events List) (44), involving home life, school, friendships, etc. In the affirmative case, the participant rates the level of stress the event caused on a 5-point scale. Collected on NPT day.

*NPT, Neuropsychological Testing*.

**Table 2 T2:** Primary and secondary outcome measures regarding the child.

**Variables**	**Instruments/scale**	**Expected outcome**

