### Data Analysis Plan

For the analysis of the primary outcome, exposed and non-exposed groups will be compared in terms of their performance on the IQ test using a linear regression model taking into account potential confounders, including antenatal exposure to MP, point in time of exposure, maternal age at birth, birth weight, and socioeconomic background. Exploratory analysis of secondary outcomes will be performed with a linear regression model. Those outcomes measured repeatedly throughout the course of the TSST-C will be evaluated as time series data with a linear mixed model, with time as a further independent factor. For this analysis, two models will be fitted to explore (1) overall mean activity throughout the TSST-C, as well as (2) the change from baseline, in which the stress response will be adjusted to the baseline value.

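### The primary IQ model does not name the collected prenatal stress score, names one term downstream of exposure and one undefined for controls, and can only estimate the association with an MP-treated relapse, not with MP alone

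*Protocol article*

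**What the plan says.** **Confounding.** Methodological Challenges states: "In this study, antenatal or postnatal stressors may act as confounders". It links maternal stress in pregnancy to "an increased risk of cognitive, behavioral, and emotional problems in later life" and describes a relapse as both a reason for glucocorticoid treatment and a heavy psychological burden. Maternal stress is estimated with an adapted questionnaire, which Table 1 shows is answered trimester by trimester.

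**Model.** The Data Analysis Plan compares IQ between groups by linear regression with "potential confounders, including antenatal exposure to MP, point in time of exposure, maternal age at birth, birth weight, and socioeconomic background". Sample Size adds: "The planned regression models include seven variables, which, based on the *rule of ten* leads to a sufficient number of cases". Matching is on age and sex.

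**Other data.** For the mother's MS, "medical files and the mother are consulted regarding disease course and duration, therapies, and disease progression" (Table 1). The week of relapse and treatment is recorded for exposed children only. The Background says antenatal glucocorticoid treatment shows itself in lower birth weight.

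**Interpretation.** Because relapses in pregnancy seldom go untreated, "there is no realistic way of mitigating this confounder using an untreated MS control group". Research Aims and Hypotheses nevertheless opens with "Fetal exposure to MP during MS relapse therapy leads to epigenetically mediated" and lists, among the decisions to be informed, MP treatment set against leaving the relapse untreated.

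**The concern.** By the article's own account, a relapse leads to MP and also raises maternal stress, and maternal stress is tied to poorer cognition in the child. That is confounding of the MP coefficient, and it runs in the direction of the study hypothesis (lower IQ in exposed children). The measured variable that could address part of it is not among the named terms.

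Two of the named terms do not do a confounder's work. Adjusting for birth weight removes from the MP coefficient whatever part of the association passes through fetal growth. Point in time of exposure does not exist for half of the sample.

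At stake is the reading of the primary result. A lower IQ in the exposed group could reflect MP, the relapse, the stress around it, or a mixture, while the stated hypothesis and one of the stated decisions treat it as MP.

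**Working it through.** **1. Terms of the model.**

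| Term | Named in the Data Analysis Plan? | What the article says about it |
|---|---|---|
| MP exposure | yes | the exposure itself, not a confounder |
| Point in time of exposure | yes | recorded for exposed children only |
| Maternal age at birth | yes | – |
| Birth weight | yes | lowered by antenatal glucocorticoids |
| Socioeconomic background | yes | – |
| Two further variables (7 − 5 = 2) | no | could be the matching factors, or stress |
| Maternal prenatal stress | no | called a confounder, and collected |

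**2. Point in time of exposure.** If it is left missing for controls, a complete-case fit drops every control and the MP coefficient cannot be estimated. If controls are given a filler value, the model is in effect IQ = b0 + b1·MP + b2·MP·(week − c). Then b1 is the group difference at week c, so it depends on an arbitrary coding choice. With c = 0 it is an extrapolation to week 0.

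**3. The plan's own power figure.** Inputs (Sample Size): difference 10.5, SD 14.0, 35 per group, α 0.05, taken as two-sided. d = 10.5/14.0 = 0.75. The noncentrality is d·√(35/2), i.e. 2.97 at d = 0.71 and 3.14 at d = 0.75, on 68 df. Power is 83.3% and 87.1%, against 82% and 87% stated. The figures reproduce closely; the point is not about them.

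**4. Size of the bias from leaving stress out.** Bias = (IQ points per SD of stress) × (group difference in SD). The documents give neither input, so both are assumptions: 1 to 5 points per SD, and 0.3 to 1.0 SD.
- Low end: 1 × 0.3 = 0.3 points, or 0.3/10.5 = 3% of the planned effect.
- High end: 5 × 1.0 = 5 points, or 5/10.5 = 48%.
- With no true MP association, the two-sided t-test (35 per group, SD 14) would reject in 5.1% of trials at the low end and 31% at the high end, instead of 5%.

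**5. Can a covariate separate MP from the relapse?** Suppose all 35 evaluable exposed children had a maternal relapse and u of 35 controls had an untreated one. The squared correlation of MP and relapse is (35 − u)/(35 + u), so the variance inflation is (35 + u)/(2u).

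| u | Variance inflation | Power at d = 0.75 (8 variables) |
|---|---|---|
| 0 | not estimable | – |
| 1 | 36/2 = 18 | 11% |
| 2 | 37/4 = 9.3 | 17% |
| 4 | 39/8 = 4.9 | 29% |

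In practice they cannot be separated.

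**6. Price of adjustment.** Take N = 70 and 8 variables, and let R² be the share of MP exposure explained by the other covariates (assumed). The standard error in SD units is √[(4/70)/(1 − R²)], on 61 df. No gain from explained IQ variance is credited.

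| R² | Power, d = 0.71 | Power, d = 0.75 |
|---|---|---|
| 0 | 83% | 87% |
| 0.1 | 79% | 83% |
| 0.3 | 69% | 73% |
| 0.5 | 54% | 59% |

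**7. Variable count after the change.** 7 − 2 (birth weight, point in time) + 1 (stress) = 6 at most, and 70/6 = 11.7 children per variable, within the plan's own rule. Adding two MS terms in a sensitivity model gives 8, and 70/8 = 8.75.

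**The case against.** The strongest reply is that the covariate list is open. It begins with the word *including*, two of seven variables are unnamed, and an article may leave the full list to an analysis plan that is not shown. This stands as far as it goes: omission of the stress score from the final model is not proven. It does not dispose of the point, because the article did choose terms to name. It named a downstream variable and one undefined for controls, and passed over the factor it discusses at length as a confounder.

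Second, the limitation is disclosed, and the primary objective is worded as an association. Both are true. But the article never says that the stress score enters the model, and the hypothesis and the decision aims still speak of MP.

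Third, leaving the stress score out of a primary model is defensible. It is recalled at least 8 years later by mothers who know whether they relapsed, and stress may partly result from the relapse. This stands, and it argues for showing both estimates rather than one.

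Some stronger readings go beyond the documents:
- A reader might infer that DMT exposure and MS activity are established confounders as well. The article says of stopping DMT only that "treatment is usually discontinued with a subsequent risk increase for relapses". It states no effect of DMT or maternal disease activity on child cognition, and nothing shows that the groups differ in DMT.
- A reader might ask for pre-conception relapse counts or a cumulative-dose analysis. The article does not show that either item is collected.
- A reader might ask for tighter matching of the remaining controls. Inclusion began in October 2020, so this would mix two matching schemes.

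**Conclusion.** The point holds in a limited form. Three things are established from the article: the stress score is collected and is treated as a confounder but is not named in the primary model; birth weight and point in time of exposure are poor choices for a between-group model; and the contrast is MP-treated relapse against largely no relapse, which adjustment cannot undo.

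It is not established that stress is absent from the final model, nor that the result is biased by any given amount. The range of 0.3 to 5 IQ points (3% to 48% of 10.5) rests wholly on assumed inputs. Its low end is trivial; its high end would matter for the primary conclusion. The limit on interpretation needs no such assumption, since it follows from the article's own statement that relapses seldom go untreated. The model terms and the wording should be settled before the analysis.

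**What to change.** 1. Name all seven variables of the primary model.
2. Drop birth weight and point in time of exposure from the between-group model. Time of exposure may be examined within the exposed group.
3. Report the MP coefficient with and without the maternal prenatal stress score, and state in advance which of the two carries the primary test.
4. Add a sensitivity analysis with the MS course and therapy data already collected.
5. State the estimand and the conclusion as the association with an MP-treated relapse, not with MP alone, and do not present the result as an answer to MP against an untreated relapse.

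The cost is analysis-plan text and data already planned for collection. Precision falls if the added covariates correlate with MP (at R² = 0.3, power is 69% to 73%). The sensitivity model, with 8 variables, falls slightly below ten children per variable. The stress-adjusted estimate has its own weaknesses, long recall and possible dependence on the relapse, so it should stand beside the unadjusted one rather than replace it.

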## Ethics and Dissemination

This study is conducted with the approval of the ethics committees of Friedrich-Schiller University Jena (reference: 2020-1668-3-BO) and the medical faculty of Ruhr University Bochum (reference: 21-7192 BR). The results are going to be published in relevant peer-reviewed journals, presented in accordance with the STROBE 2007 Statement (57).

